### Diagnostic criteria for MCI and AD

The chosen definition of AD was based on the criteria of the National Institute of Neurological and Communicative Diseases and Stroke and the AD and Related Disorders Association (NINCDS-ADRDA) [43]; this can diagnose AD as possible, probable or certain. The severity of dementia was based on the MMSE score [8]. Subjects were categorized as being in the mild stage if their score was between 25 and 21, in moderate stage if their score was between 20 and 10 and in the severe stage if their score was below 10.

The diagnostic criteria for MA at a stage of dementia were the clinical criteria for probable AD [43,44].

At the stage of pre-dementia (corresponding to the amnestic MCI diagnosis [15-17,45]), diagnostic criteria were the clinical criteria of the Pre-Al study and the paraclinical criteria recently proposed for research [46,47]. For other disorders frontotemporal lobar degeneration [48], lewy body dementia [49] and vascular dementia [50] criteria were those referenced.

### Examination procedure: baseline assessment and follow-up

1. Baseline assessment: cognitive tests at HEC

The cognitive assessments were performed by trained physician and nurses. A guide, detailing how to perform the cognitive tests, specified the order in which the tests should be performed. Immediate recall and cued free test of five words was performed by the doctor, then an intercurrent test of attention for about 10 minutes and finally a free and cued delayed recall test of five words. The attention of the subject was intentionally diverted using several tests. For example, drawing pentagons as part of the MMSE and a visual-construction task in the Cognitive Assessment Battery (CAB 96) [51]. Time orientation questions (‘What day of the week is it?’; ‘What month is it?’; ‘What year is it?’), questions about drug intake (the number of therapeutic classes attended, the use of a psychotropic drug and treatment for osteoporosis), the TUG [23] and the imagined TUG were also used. The Instrumental Activities of Daily Living (IADL) scale (derived from the IADL by Lawton and Brody [21]), was used to evaluate functional capacity. This test explores the subject’s degree of autonomy or dependence in relation to four practical activities of daily life (telephone use, transportation, responsible administration of medication and budget management). The three-word test, the simplified clock test, the five questions about spatial orientation and verbal fluency tests were then performed by the nurse.

2. Baseline assessment: memory consultation at MC

An appointment for consultation at the MC was made at the end of the periodic health examination. If this had not been possible, the patient was contacted by a secretary of the HEC to schedule the appointment. The standardized biological check-up performed at HEC included a neuropsychological assessment, screening for syphilis, serum electrolytes determination and serum assays of vitamin B12, vitamin B9, albumin, pre-albumin and Thyroid Stimulating Hormone (TSH). Depression screening was performed using the Geriatric Depression Scale (GDS); a 15-item scale of depressive symptomatology suitable for elderly patients [52].

Check-ups at the University Hospital of Lyon were supplemented by the Hamilton Anxiety Scale, a questionnaire on therapeutic compliance and nutritional assessment. The established diagnosis, according to the criteria specified above, was sent to the doctor working at the HEC so that they could classify patients as “normal” subjects, subjects with MCI or subjects with dementia. A MRI scan was systematically performed at the University Hospital of Angers. At the University Hospitals of Lyon and Saint-Etienne, MRI scans were reserved for subjects where anomalies were detected during the examination.

3. Follow-up at MC

Subjects of the study will be re-called one year later (T1) at MC for a second neuropsychological check-up using the same protocol as at T0.

### Collection and data quality control

Collection and data entry are managed by the HEC of Lyon; collected data is entered by two secretaries of the HEC who have been trained in data management (double input). The collection tool was developed by the Regional Medical Service Officer (RMSO) of the Rhône-Alpes region.

### Main outcome measure

Patients will be recorded as belonging to one of three groups: “normal”, MCI or dementia subjects. The main outcome measure will be the diagnosis of MCI or AD and related disorders at T0 and T1. The secondary outcome measure will be falls at T0 and T1. A fall was defined as an event which results in a person coming to rest unintentionally on the ground, floor or at a lower level.

### Statistical analysis

Baseline characteristics of the subjects (for example, age and sex) will be described as above. Continuous variables will be summarized by the mean and standard deviation or the median and interquartile range (as appropriate). Categorical variables will be summarized as proportions of each category.

Socio-demographic and clinical comparisons will be performed between three groups (normal, MCI and dementia subjects). Group proportions will be compared using Pearson’s chi-squared test. The means of these groups will be compared using an Analysis of Variance (ANOVA) with parametric and nonparametric tests, depending on the distribution of the variables. We will study the relationship between the result of each cognitive test performed at HEC and the diagnosis confirmed by the memory consultation. A Receiver Operator Characteristic (ROC) curve will be generated for each cognitive test, using MCI and AD and related disorders diagnosis as references. The optimum threshold, providing the best compromise between sensitivity and specificity, will therefore be determined. Predictive and negative values, as well as positive and negative likelihood ratios, will be calculated. We will use a binary or multinomial logistic regression to determine which test, or combination of cognitive tests, are the most predictive for MCI and AD and related disorders diagnosis. Models will be adjusted for potential confounding variables.

A p value less than 0.05 will be considered as statistically significant.

Statistical analyses will be performed using SPSS (Statistical Package for the Social Sciences) version 17.0 for Windows (SPSS Inc., Chicago, Illinois, USA).

### Inclusions

Inclusions at HEC took place from 15th November 2009 to 31st December 2011 (Figure 2). The one-year follow-up will end during the first semester of 2013.

**Figure 2 F2:**
[figure not shown]
**EVATEM study flowchart.** MC: Memory Complaint, ES: elderly subjects. A: Angers, SE: Saint-Etienne, L: Lyon.

A total of 4571 elderly subjects aged 65 years or over were eligible for research into the diagnosis of memory complaints. Amongst those subjects, 57.5% were recruited by the HEC of Lyon, 34.2% by the HEC of Angers and 8.3% by the HEC of Saint-Etienne.

The percentage of subjects with memory complaints, detected using the self-administered questionnaire (Q1), was 70% for the HEC of Angers and 59.4% for the HEC of Saint-Etienne. At the HEC of Lyon, where memory complaints were screened using a questionnaire administered by doctors (Q2), the percentage of complaints was 27.5%. Cognitive tests were refused by 33.6% of people with memory complaints. Amongst the 832 subjects for whom an appointment at MC had been made, 74.5% attended a consultation. Thus, the final study population included 620 subjects.

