**Method/design:**

The EVATEM (*évaluation des troubles de l’équilibre et de la mémoire* (evaluation of balance and memory problems)) cohort study was designed to prospectively assess the predictive value of tests for the diagnosis of mild cognitive impairments and Alzheimer’s disease in elderly subjects aged 65 years or over. Subjects were recruited from three health examination centers that are part of the French health insurance system. If a memory complaint was identified (using a dedicated questionnaire), the five-word test, the cognitive disorders examination test and the verbal fluency test were administered during a preventative consultation. A memory consultation was performed at a University Hospital to diagnosis any potential cognitive disorder and a one-year follow-up consultation was also scheduled. We recorded 2041 cases of memory complaint at our Health Examination Centers. Cognitive tests were refused by 33.6% of people who had a memory complaint. The number of subjects sent to a University Hospital memory consultation was 832 and 74.5% of them completed this consultation. The study population therefore includes 620 subjects.

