## Methods/design

### Study design

This is a prospective multicenter cohort study with a one-year follow-up. Tests were carried out at two types of medical organizations: HEC and MC. HEC are structures belonging to the French health insurance system which offers check-ups and screening for the prevention of health conditions, health education and actions, and chronic disease support. This is a free check-up and priority is given to frail or vulnerable people. MC (as defined by the circular issued by the *Direction Générale de l’Offre de Soins* (DHOS) (general directorate for healthcare provision) on 16^th^ April 2002) offer consultations and day hospitalizations which are dedicated to medical diagnostics, follow-up and nursing (treatments both with and without the administration of drugs). MC are responsible for research on AD and related disorders, participate in academic training and coordinate an interregional plan for local memory consultations.

The three HEC which participated in the EVATEM study are located in three French cities: Lyon Angers and Saint-Etienne. The diagnostics were performed through three MC in the academic hospitals of these three cities. The study is composed of several steps (Figure 1). Patients with a memory impairment were identified at HEC using questionnaires and cognitive tests during periodic health examination at T0. Memory consultations to diagnose MCI and AD and related disorders were carried out at MC according to a standardized neuropsychological evaluation and complementary exam at T0. A one-year follow-up exam, at T1, was scheduled for each of the patients.

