### Population

Subjects were selected during free periodic health examinations in one of the three health examinations centers that participated in this study. These HEC were located to the cities of Lyon, Angers and Saint-Etienne.

Patients could be included if they were 65 years of age or older, lived at home or in a non-medical institution, volunteered to participate to a periodic health examination and if a memory impairment concern was identified (either by the patient themselves or by a member of their family).

Patients were excluded from the study if they had dementia, an inadequate level in French language ability, to a sensory deficiency which would compromise their evaluation.

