### Sample size

We calculated the required sample size need to detect an expected sensitivity and specificity of 0.9 with the cognitive tests used in the HEC.

We set the minimum acceptable lower 95% confidence limit at 0.75, with a 0.95 probability.

Using the table of Flahault *et al.* 70 confirmed cases were required [19]. The number of controls required was calculated to be 513 with the equation: N controls = N cases [(1-P)/p] [19]; where p was the expected prevalence of MCI or AD and related disorders (we supposed this to be 12% [13])_._ The total target sample size was therefore 583.

We predicted the loss of subjects between examinations in the HEC and the MC to be 30% and so aimed to recruit 833 subjects. Actual recruitment was consistent with these estimates.

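### Sensitivity, specificity, likelihood ratios and thresholds will rest on the 620 memory-clinic attenders only, so they are at risk of partial-verification bias of uncertain direction

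*Protocol article*

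**What the plan says.** The abstract and the Inclusions section of the protocol article give the flow. "We recorded 2041 cases of memory complaint at our Health Examination Centers". Of these people, "Cognitive tests were refused by 33.6% of people with memory complaints". Then "Amongst the 832 subjects for whom an appointment at MC had been made, 74.5% attended a consultation". The section concludes: "Thus, the final study population included 620 subjects".

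The Statistical analysis section relates each health examination centre (HEC) test to the diagnosis made at the memory clinic. From this it derives ROC curves, an optimum threshold, predictive values and likelihood ratios. Only people who attended the clinic can enter these calculations.

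The article is not clear on what led to referral:
- Study design: "Patients with a memory impairment were identified at HEC using questionnaires and cognitive tests during periodic health examination at T0".
- Population and Data collection: entry depends on a memory concern, shown by at least one positive questionnaire answer. No test score is mentioned.
- Examination procedure: the clinic appointment was arranged when the health examination ended, hence after the tests. No cut-off is given.
- Population also states: "Patients were excluded from the study if they had dementia". It excludes inadequate French and sensory deficiency as well.

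The Sample size section allows for a 30% loss between HEC and clinic and adds: "Actual recruitment was consistent with these estimates".

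**The concern.** When the reference diagnosis is obtained in only some of those tested, sensitivity and specificity among the verified equal the true values only if verification is unrelated to the test result and to disease. Otherwise the estimates shift, and the likelihood ratios and the ROC-based threshold shift with them. Inflating the sample size for loss protects precision but does nothing about this.

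The article gives grounds for asking the question. The appointment followed the tests, and the Study design wording can be read as making the tests part of how people were selected. The Discussion describes avoidance of consultations through fear of diagnosis. The text does not explain the gap between those who did not refuse the tests and those given an appointment, and it states no comparison of verified with unverified people. The operating points are a main product of the study and are meant to support a recommendation to the HEC.

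**Working it through.** **Inputs.** From the abstract and Inclusions section: 2041 complaints, 33.6% refusal, 832 appointments, 74.5% attendance, 620 analysed. From the Sample size section: 12% prevalence, expected sensitivity (Se) and specificity (Sp) 0.90, 30% loss, targets of 583 analysed and 833 recruited.

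**Flow.**
- 620 / 832 = 74.5%, which reproduces the article's figure. Not attending: 832 − 620 = 212 (25.5%).
- Not refusing the tests: 2041 × (1 − 0.336) = about 1,355 (1,354 to 1,356 allowing for rounding of the percentage).
- Of these, without an appointment: 1,355 − 832 = about 523.
- With a reference diagnosis: 620 / 1,355 = 45.7%.

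**Planned loss.** 583 / 0.70 = 833, so the target reproduces. Recruitment was 832 against 833, loss 25.5% against 30%, and the analysed number 620 against 583.

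**Bias formulas.** Let R be the probability of verification in test-positives divided by that in test-negatives, with verification depending only on the test result:
- apparent Se = Se·R / (Se·R + 1 − Se)
- apparent Sp = Sp / (Sp + (1 − Sp)·R)

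**Largest possible R on the 832.** Assume Se = Sp = 0.90 and 12% prevalence.
- Share testing positive: 0.12 × 0.90 + 0.88 × 0.10 = 0.196.
- If every test-positive attended, attendance in test-negatives would be (0.745 − 0.196) / 0.804 = 0.683.
- R therefore cannot exceed 1 / 0.683 = about 1.46.

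**Results on the 832 (assumed true 0.90/0.90).**

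| R | Apparent Se | Apparent Sp |
|---|---|---|
| 0.75 | 0.675/0.775 = 0.87 | 0.9/0.975 = 0.92 |
| 1 | 0.90 | 0.90 |
| 1.25 | 1.125/1.225 = 0.92 | 0.9/1.025 = 0.88 |
| 1.46 (ceiling) | 1.318/1.418 = 0.93 | 0.9/1.046 = 0.86 |

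The true positive likelihood ratio is 0.90/0.10 = 9.0. It would read about 11.3 at R = 0.75 and about 6.6 at the ceiling.

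With assumed true values of 0.80/0.80, the share testing positive is 0.272. Test-negative attendance cannot then fall below (0.745 − 0.272) / 0.728 = 0.65. The ceiling is R = 1.54, giving 0.86/0.72.

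**If the 523 were all eligible and tested.** Larger ratios become possible. With 0.90/0.90, R = 2 gives 0.947/0.818 and R = 3 gives 0.964/0.750. The text does not establish that these people belong in the denominator.

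**Predictive values.** If verification depends only on the test result, the probability of disease given that result is the same in verified and unverified people. Under the assumptions above, the positive predictive value at a fixed threshold is 0.108/0.196 = 0.55 whatever R is.

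**The case against.** A reader might infer that the estimates are known to be biased, with sensitivity too high and specificity too low. The article does not support this. It never says that appointment or attendance depended on a test score, and the Study design sentence is only ambiguous. A design of 70 cases and 513 controls at 12% prevalence fits referral of everyone with a complaint better than referral by test result. The two routes that the article does suggest, fear of diagnosis and exclusion of dementia, would tend to remove poor performers and so push the bias the other way.

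A reader might also take 1,355 as the proper denominator and about 54% as the true loss. That figure is complaints less refusals, not a count of eligible tested people. Some of the 523 may be exclusions or people who did not consent. The Discussion mentions many exclusions in Lyon, and the Figure 2 flowchart, not available in the text at hand, may account for them. Only the 212 are certain.

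Nor is the recruitment statement in the Sample size section wrong: it matches the plan when loss is counted from the appointment.

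Finally, the article's stated aim is predictive values, which are largely protected at a fixed threshold, as is a correctly specified logistic model that includes the tests governing verification. A fuller analysis plan, not shown, may also deal with missing reference diagnoses.

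All of this stands, and it limits the size of the concern. It does not remove it. The article itself fixes the population at 620 and plans ROC thresholds and likelihood ratios in it, and these are not protected in the same way. Predictive values quoted at a threshold taken from a distorted ROC curve would also belong to a different threshold from the one intended.

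**Conclusion.** The concern holds as a risk of partial-verification bias, of uncertain direction and unknown size, in sensitivity, specificity, likelihood ratios and ROC thresholds.

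On the certain loss of 212 among 832, with assumed true values of 0.90/0.90 and 12% prevalence, the effect runs from none (R = 1) to 0.93/0.86 at the ceiling of R = 1.46. If poor performers stay away, R = 0.75 gives 0.87/0.92. The positive side of this range is bounded by the attendance figures. The value 0.75 is only an illustration. Larger effects need some or all of the 523 to be eligible, consenting and tested, which the text does not show.

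The calculation assumes that verification depends only on the result of the test in question. If it also depends on disease, or on another test, these bounds and the protection of predictive values no longer strictly apply. No corrected estimate can be computed here, because the article gives no test results for unverified people.

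**What to change.** 1. Reconcile the Study design section with Population, Data collection and Examination procedure, and state whether HEC test results played any part in referral.
2. Account in the text for the steps from about 1,355 to 832 to 620, separating exclusions, non-consent and non-attendance. Tabulate HEC test scores by verification status.
3. Add a verification-corrected analysis, specified before results are seen, in the 832 referred. Extend it to any other eligible, consenting, tested people. Begg-Greenes, inverse-probability weighting or multiple imputation would serve, using the three test scores, age, sex, centre, EPICES, mini-GDS and IADL. Report it beside the 620 complete-case result. If the two differ materially, base the HEC threshold recommendation on the corrected estimate.
4. In the Sample size section, add only that the 25.5% loss is counted from the appointment. The statement needs no other correction.

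The Data collection and Examination procedure sections list these variables as collected at the HEC, so the cost is mainly analysis time. The authors should first confirm that usable, consented records exist for non-attenders. The correction assumes that verification is ignorable given the HEC data, which cannot be tested from those data, and confidence intervals will be somewhat wider.

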## Discussion

The EVATEM study will identify which one, or which combination, of these studied tests are the most predictive of MCI and AD and related disorders. This will provide a recommendation as to which should be performed on elderly patients reporting a memory complaint during a health examination at HEC.

The age for inclusion selected for the EVATEM study was 65 years old and more as the prevalence of AD is low before the age of 65 years [53]. This age criterion was also used in the PAQUID study [54] and in a three city study [55].

HEC recruit elderly patients from those listed in the files of the French health insurance system. Previous studies have compared elderly individuals using HEC to those of the general population of the same age. It appears that people over 60 years old who consult at HEC are more likely to be young male seniors (60 to 70 years old), living in couples, individuals with a healthy lifestyle (lower tobacco consumption, lower alcohol consumption and more physic activity) and those that consult more frequently than the corresponding general population (data unpublished, CETAF). However, it was previously thought that the population attending HEC was not fundamentally different from the general population of elderly persons aged over 60 years who were living at home and not suffering from disabilities.

The fact that patients agreed to participate to a periodic examination suggests that they take an interest in their health and may therefore also be more likely to attend cognitive impairment screening. Use of the Q1 questionnaire may lead to a self-selection bias associated with the fear of diagnosis, especially if another family member is suffering from AD. Representations of this type of disease and people with AD in our society are extremely negative. Consequently, patients may delay, as long as possible, addressing the issue of a disease that “crystallizes all the fears associated with aging” [6]. Societal representations lead to denial behavior and avoidance of medical consultations as the fear of diagnosis is associated with a set of losses including identity and dignity [56,57]. The administration of Q2 by doctors from Lyon led to a high selectivity in the screening of memory complaints. It will be interesting to compare the diagnostic and predictive values of the tests that result from these two groups.

This study, which began in late 2009, is based on the 1984 criteria for the clinical diagnosis of AD. In the revised NIA-Alzheimer’s Association criteria (May 2011), a semantic and conceptual distinction is made between AD pathophysiological processes and the clinically observable syndromes that result (this distinction was blurred in the 1984 criteria [58,59]). According to the revised criteria, the clinical and cognitive evaluation for MCI due to AD is almost identical to the one previously described by Petersen *et al.*[59]. All patients who would have been classified under “probable AD” by the 1984 NINCDS–ADRDA criteria would be likely to meet the current criteria for probable AD dementia. The predictive values of the three cognitive tests for the diagnosis of a mild amnesic cognitive impairment, in turn predictive of AD, will be analyzed.

The use of cognitive tests can be limited by language barriers; only people with a good level of French had been included in EVATEM. There were a particularly high number of exclusions in Lyon and it would be interested to develop a translation of the selected tests.

This study provided an opportunity for each HEC to establish care pathways with their closest MC and for medical and paramedical staff to be educated in the early diagnosis of related disorders [5]. Specific training, carried out by MC geriatricians, was required. This was well received and has demonstrated that cognitive tests can be easily integrated into a preventive consultation.

The participants of this study will be re-examined one year after their inclusion; this will enable us to estimate the predictive abilities of the tests to diagnose MCI and dementia. The use of simple tests with good predictive abilities should help guide patients from centers of prevention to MC for early medical and behavioral care management.

Further research projects are planned using the EVATEM database. These include studying the relationships between insecurity and memory complaints, cognition and anxiety-depression, cognition and walking, and cognition and vitamin D levels.

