**Discussion:**

Tests for the early diagnosis of a mild cognitive impairment or Alzheimer’s disease and related disorders should be used in centers dedicated to disease prevention. These should guide subjects with memory impairment to full memory consultations at hospitals and improve the access to early medical and behavioral support.

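### The recommendation rests on which test ranks most predictive and is never tied to the 0.75 lower confidence limit on which the study was sized

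*Protocol article*

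**What the plan says.** Three parts of the protocol article bear on this.

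- **Sample size.** The study is sized to "detect an expected sensitivity and specificity of 0.9 with the cognitive tests used in the HEC". The criterion is: "We set the minimum acceptable lower 95% confidence limit at 0.75, with a 0.95 probability". From it the article derives that "70 confirmed cases were required", then 513 controls at an assumed 12% prevalence, 583 in total and 833 to recruit.
- **Statistical analysis.** Each test gets a ROC curve, and "The optimum threshold, providing the best compromise between sensitivity and specificity, will therefore be determined". Predictive values and likelihood ratios follow. Logistic regression then decides which test or combination predicts best. The only numerical criterion is p below 0.05. The section does not mention 0.75, a confidence interval for sensitivity or specificity, or any other minimum accuracy.
- **Discussion.** The study is to identify the most predictive test or combination, and "This will provide a recommendation as to which should be performed on elderly patients reporting a memory complaint". No condition is attached, and no outcome is described in which none is recommended.

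The Background and the later part of the Discussion speak of good predictive power or ability. Neither gives a figure or links it to the recommendation.

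**The concern.** The design states what accuracy is acceptable, and the route to the conclusion does not use it. Ranking is relative: it shows which candidate is best, not whether the best is good enough. The p-value does not fill the gap, because it tests for any association with the diagnosis and not for adequate accuracy.

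At stake is what health examination centers would be told to do. If the three tests are only moderately accurate, the text as it stands leads to a recommendation for routine use of a test that the sponsor's own criterion would reject. The 70 cases and the 0.95 probability were bought for a comparison that the analysis does not make.

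**Working it through.** **Inputs.** From Sample size: expected sensitivity and specificity 0.90, lower limit 0.75, probability 0.95, prevalence 12%, loss 30%. From Inclusions: 620 subjects in the final population.

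**1. The plan's own figures.** Find the smallest n for which P(Clopper-Pearson lower limit ≥ 0.75 | true value 0.90) ≥ 0.95.

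- One-sided 95% limit: n = 70. The limit is reached with at least 59/70 correct (84.3%), which has probability 0.956 at a true 0.90 and 0.044 at a true 0.75.
- Two-sided 95% interval (2.5% in the tail): n = 85. At n = 70 at least 60/70 are needed, with probability 0.913.
- Controls: 70 × 0.88/0.12 = 513.3, so 513. Total: 70 + 513 = 583. Recruitment: 583/0.70 = 832.9, so 833.

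All four figures reproduce. The 0.75 limit is therefore a working criterion of the design, read as a one-sided limit.

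**2. What the limit would demand.** With 70 cases and 513 controls and one-sided limits, a test needs at least 59/70 for sensitivity and 402/513 (78.4%) for specificity. The probability that one test passes on sensitivity is 0.005 at a true 0.70, 0.044 at 0.75, 0.232 at 0.80, 0.644 at 0.85 and 0.956 at 0.90.

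**3. Whether p < 0.05 could stand in for it.** Take a test with sensitivity 0.50 and specificity 0.70, with 70 cases and 513 controls. It reaches p < 0.05 with probability about 0.91. Its positive predictive value at 12% prevalence is 0.12 × 0.50 / (0.12 × 0.50 + 0.88 × 0.30) = 0.060/0.324 = 18.5%. A test with 0.60 and 0.60 reaches significance with probability about 0.89, and its positive predictive value is 0.072/(0.072 + 0.352) = 17.0%. Either has essentially no chance of meeting the 0.75 limit.

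**4. The ranking as described.** At 12% prevalence, 620 subjects give 620 × 0.12 = 74.4 and 620 × 0.88 = 545.6, taken as 74 cases and 546 non-cases. Assumptions: three equally accurate tests, binormal scores, within-class correlation 0.3 to 0.6, 400 studies per setting. In each study the test with the highest AUC is taken at its Youden cut-off.

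| True AUC of all three tests | Top test has p < 0.05 | Both lower limits ≥ 0.75 |
|---|---|---|
| 0.50 | about 5–6% | 0% |
| 0.60 | about 95–98% | 0% |
| 0.70 | 100% | 0% |
| 0.80 | 100% | 0% |
| 0.90 | 100% | about 30–40% two-sided, 52–56% one-sided |
| 0.965 (sensitivity = specificity = 0.90) | 100% | about 98% two-sided, above 99% one-sided |

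At AUC 0.70 the top test's apparent sensitivity and specificity are about 0.70 and 0.66.

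**5. Optimism from choosing on the same data.** A single test with true values of 0.90 at a cut-off fixed in advance meets both limits in about 0.97 of studies one-sided, or 0.88 two-sided. After picking the cut-off and the best of three on the same data, the rates are above 0.99 and about 0.96–0.98. Apparent sensitivity then averages about 0.93 against a true 0.90. A bar applied to uncorrected limits would be too easy to pass.

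**The case against.** The sentence on the recommendation is a statement of purpose in the Discussion, not a formal decision rule. The stated aim is to evaluate predictive values, and sensitivity, specificity, predictive values and likelihood ratios are planned or implied for each test, so poor accuracy would be visible to a reader. The article is a condensed protocol, and a fuller plan might apply the limit. These points are fair, and they reduce the weight of the concern. They do not remove it: the article states a criterion, a way of selecting and what the selection leads to, and the last two pass over the first. That is more than a detail left out.

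Two stronger readings are tempting, and the document supports neither.

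- A reader might infer that the study cannot end in a negative answer. That a ranking always has a top entry is true by definition and measures nothing. The article does speak of good predictive ability, and the planned estimates could show that it is lacking. What is missing is a figure and a link to the recommendation.
- A reader might infer that the Abstract prejudges the result by saying that tests "should be used in centers dedicated to disease prevention". The subject of that sentence is early-diagnosis tests in general. It neither names the three study tests nor reports a result for them.

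It is also fair to object that simply applying 0.75 to ordinary limits would ignore both the sidedness of the limit and the optimism shown in step 5. That stands, and the fix deals with both.

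**Conclusion.** The concern holds in limited form. The 0.75 limit governs the sample size but appears nowhere in the selection of a test or in the basis for the recommendation. A significant test well short of that limit could therefore be recommended. Tests with AUC 0.60 to 0.80 show the size of the gap: the top test is significant in about 95% of studies or more, and meets the plan's own limit in 0%.

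The simulated figures assume 12% prevalence among the 620 subjects, binormal scores, equal accuracy and the stated correlations. The 0% at AUC 0.70 holds for one-sided and two-sided limits alike. No planned estimate is wrong because of this point, and the sample size is correct under a one-sided limit. The weakness lies in how the results become a recommendation.

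**What to change.** - **Statistical analysis:** report lower confidence limits for the sensitivity and specificity of each test or combination at its chosen cut-off. Correct them for choosing the cut-off and the test on the same data, for example by bootstrapping the whole selection.
- **Sample size and Statistical analysis:** state that the limit is the one-sided 95% limit, which reproduces 70 cases. If a two-sided interval is meant, acknowledge that 70 cases give probability 0.913 and not 0.95.
- **Discussion:** make the recommendation conditional on both lower limits reaching 0.75, rank only the candidates that qualify, and allow the conclusion that none is recommended. Sample size speaks only of the tests, so say that the limit applies to combinations too, since a combination may be recommended.

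The cost is some additional analysis and a few sentences, with no new data. The downside is that the study may end without a recommended test. The one-year follow-up was still to finish when the article was written, so the rule could be fixed before the final analysis.
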